### Study population

The same study population will be used for the primary and secondary aims. Entry to our study will be on survey completion date for women who participated in the ALSWH survey waves between 2004 and 2008 or the 45 and Up Study baseline survey between 2006 and 2009 or the date of the Rotterdam Study interview and clinical examinations for women who completed these between 2004 and 2008. Inclusion criteria will be women who at entry to our study (1) were alive and consented to linkage of administrative data, (2) have evidence of hypertension from either self-reported hypertension (Australian longitudinal cohorts) or have a recorded diagnosis of hypertension in clinical examination data (Rotterdam cohorts).

Women will be excluded at entry if they had (1) history of primary invasive/in situ breast cancer or cancer that is metastatic to the breast; or (2) history of bilateral mastectomy; or (3) evidence of CCB use prior to entry. Further exclusion criteria will be applied in Australian longitudinal cohorts only as per standard practice when using PBS data: (1) women with any evidence of being Department of Veterans’ Affairs (DVA) concession card holders, because DVA-subsidised prescriptions are funded separately and not captured in the PBS data held; or (2) women who did not have evidence of concessional healthcare status for more than 1 year during period from 2003 to 2012. Those with concessional status, for example, those receiving the aged care pension or certain other government benefits, have lower copayments for PBS-listed medicines in comparison to ‘general beneficiaries’. This exclusion is necessary because some AHT medicines fall below the PBS copayment threshold for general beneficiaries, hence attracted no government reimbursement and were not captured in PBS data prior to an administrative change in 2012.^30^ In contrast, the lower copayment threshold for concessional patients means that AHT medicines can be captured throughout the study period.

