### Exposure ascertainment

The exposure in this study, for both the primary and secondary aims, will be CCB dispensing including both combination and monotherapy products. Exploring the impact of confounding by indication for non-CCB AHT medicines is important because a modest increased risk of cancer in individuals with hypertension has been documented.^33^ To avoid this issue, previous studies have used a comparator group of patients exposed to other AHTs and/or with a hypertension diagnosis.^34^ Our study population is defined by the presence of hypertension since comparing only to a reference AHT medicine group risks biasing towards the null, if the comparator drug is associated with the outcome. Thus, to reduce bias to the null, women who are both AHT and CCB naïve will be included in the study as long as they meet the entry criteria of hypertension at baseline as described previously. To ensure that exposure to other AHT medicines is accounted for, the cumulative dose-duration exposure of other prescribed AHT medicines (combined) will be captured in the same way as that described for CCB exposure. Thus, in our study, the following four exposure states will be possible during follow-up: (1) women with no exposure to either CCBs or other AHTs; (2) women exposed to other AHTs but not exposed to CCBs; (3) women exposed to CCBs but not exposed to other AHTs and (4) women exposed (at any time) to both CCBs and AHTs. To compensate for immortal-time bias, and to be able to capture the dose–response nature of the association of CCB exposure with risk of breast cancer, a time-varying continuous ascertainment of cumulative exposure (dose duration) to CCB (and separately other AHTs) will be captured as follows.^35^

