Since the CCB exposure variable will be continuous rather than binary a generalisation of the binary propensity score, the generalised propensity score (GPS) developed by Hirano and Imbens will be used.^48^ Since CCB exposure will be sporadic, we will also evaluate the dose-duration response effect by further extending the multivariable models to incorporate a time-dependent dose–response component.^49^ Specifically, the dose-duration response function will be estimated after adjusting for covariate imbalance by using the GPS methods applied in previous publications.^49–52^ The non-linear predictive relationships between the dose duration of CCB exposure and breast cancer will be modelled using non-linear threshold models developed by Gannon *et al*.^53^ Threshold models allow for the differential effect of the dose duration of CCB exposure on the incidence of breast cancer with respect to an individual’s duration and cumulative exposure to CCBs. The model will allow the coefficient (β) to vary according to the days/months/years per unit of the cumulative dose duration while assuming that other components in the model are constant across all individuals to identify the thresholds for subpopulations.^54^ The estimation of the threshold models involves searching all possible values of the dose-duration function with maximum likelihood estimators computed for every tried value. For practical purposes, the number of subpopulations will be limited to 3 or less.^54^ The threshold model that minimises the Bayesian information criterion used for selection of the non-linear models will be the final model. The counterfactual, individuals with no CCB exposure, will also be analysed as a baseline to show the impact of no versus any treatment using standard binary propensity score matching of those exposed versus non-exposed.^51^

*Secondary aim:* for the secondary aim, we will explore relationships between dose duration of CCB use and incident breast cancer and factors that confound and modify these relationships. Using multilevel modelling techniques and time-varying covariates, we will quantify the contributions of person-related, temporal-related and geospatial level-related factors to variation in the dose-duration effect. This will allow the development of both intercountry-specific and intracountry-specific profiles of women who are at higher and lower risk of CCB-attributable breast cancer.

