### Sample size calculation

Breast cancer is a relatively common event for the studies under investigation; thus, our sample size will be based on the women exposed to CCBs (as indicated by the numbers on the right-hand side of figure 3). Using a conservative ratio of unexposed:exposed of 5:1, we have 95% confidence with 80% power to detect a minimum effect size of ±0.2 for breast cancer associated with CCB use in all datasets given the number of exposed individuals.

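### The continuous propensity score is specified with no provision for women at zero CCB exposure, so the adjusted dose-response can be distorted in either direction

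*Protocol article*

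**What the plan says.** Under Statistical analysis, the reason given for the method is: "Since the CCB exposure variable will be continuous rather than binary". On that basis "the generalised propensity score (GPS) developed by Hirano and Imbens will be used", and "the dose-duration response function will be estimated after adjusting for covariate imbalance by using the GPS methods applied in previous publications". The same paragraph adds a comparison of women with and without CCB exposure, "using standard binary propensity score matching of those exposed versus non-exposed". The paragraph before it provides ordinary covariate adjustment for time-varying covariates and for any covariate that the score fails to balance.

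Other sections determine what the exposure looks like:

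- Study population excludes women with "evidence of CCB use prior to entry".
- Exposure ascertainment states that "women who are both AHT and CCB naïve will be included in the study". Two of its four exposure states have no CCB. Never-users also receive a value for time since last exposure, namely their whole follow-up.
- Sample size calculation works from the number exposed: "Using a conservative ratio of unexposed:exposed of 5:1".

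**The concern.** A continuous conditional density describes how much exposure a woman has when every amount is possible and no single value carries positive probability. Cumulative CCB exposure here has a large group at exactly zero and a skewed positive part. What makes a woman ever start a CCB need not be what makes a user accumulate more, and a single density ties the two together. If it does not describe the data, conditioning on it does not make women with no, some and much exposure comparable.

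The dose-response curve is half of the primary aim, and the search for thresholds runs on it. The Discussion also rests the study's causal framing on this score. A curve bent near zero could be reported as a threshold.

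**Working it through.** **1. Share at zero.** The only figure given is the 5:1 planning ratio: 5/(5 + 1) = 83.3% at zero. The detectable effect of ±0.2 quoted beside it cannot be reproduced, because the exposed counts are in a figure not shown and the effect scale is not stated. It is not needed here.

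**2. What the score must represent.** Let π(X) be the probability of any CCB use given covariates X, and f(t | X) the density of the amount among users. The true distribution is then

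- at zero: 1 − π(X);
- at t > 0: π(X) · f(t | X).

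A single normal density with mean μ(X) and standard deviation σ gives φ((t − μ(X))/σ)/σ everywhere. At t = 0 this depends on X only through the mean amount and need not track 1 − π(X). In one run below with 60% zeros, the confounders raised the chance of use but lowered the amount among users. Their correlations with exposure were 0.002 and 0.004, so a score built on the mean saw almost nothing to balance although both parts depended on them.

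**3. Null simulation.** The protocol gives none of these settings; they are assumptions:

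- 20,000 women, 100 replicates, two standard normal confounders.
- Outcome incidence 5%, log odds 0.3 per confounder, no CCB effect.
- Log-normal years of use among users, capped at 15.
- Score: one normal density for all women, then an outcome model quadratic in exposure and score with their product.

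The settings differ in the effect per confounder on log odds of use and on log amount: A 0.5 and 0.3; B 0.3 and 0.1; C 0.5 and −0.2; D as B but with 60% zeros instead of 5/6. Entries are false risk differences against zero exposure, in percentage points; the truth is 0.

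| Setting | Method | 1 y | 3 y | 5 y | 8 y |
|---|---|---|---|---|---|
| A | crude | 0.46 | 1.34 | 2.19 | 3.40 |
| A | single score | −0.63 | 2.89 | 1.47 | 1.06 |
| B | crude | 0.37 | 1.00 | 1.49 | 1.97 |
| B | single score | −1.82 | 0.71 | 0.07 | 2.54 |
| C | crude | 0.58 | 1.21 | 1.16 | −0.21 |
| C | single score | 0.96 | −0.32 | −0.88 | 0.07 |
| D | crude | 0.37 | 1.00 | 1.49 | 1.98 |
| D | single score | −0.43 | 1.42 | 1.25 | −1.67 |

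Monte Carlo standard errors of the single-score entries are at most 0.18. Absolute bias rises in 7 of the 16 cells (A at 1 and 3 years, B at 1 and 8, C at 1, D at 1 and 3) and falls in the other 9.

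**4. How the score is used matters.** With a continuous outcome (40 replicates) and the score used as a stabilised weight, slope bias in the five 5/6-zero settings was:

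| Crude | Single normal weight | Two-part weight |
|---|---|---|
| 0.128 | 0.062 | 0.047 |
| 0.115 | 0.032 | 0.009 |
| 0.031 | 0.008 | 0.003 |
| 0.135 | 0.036 | 0.021 |
| 0.068 | 0.025 | 0.024 |

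As a weight, the single score helped, and the two-part score helped at least slightly more. With 60% zeros the results were 0.133, 0.049 and 0.034 in one setting. In the other, where crude bias was almost nil, they were 0.001, 0.000 and −0.008, so the two-part weight is not uniformly better.

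**5. None versus any.** A binary propensity score (weighting, standing in for the planned matching) reduced bias from 1.41, 0.86 and 1.46 points in A, B and C to −0.02, 0.01 and 0.05.

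**The case against.** The article names neither the density nor the women to whom the score is fitted, and an analysis plan may do so. The none-versus-any matching stands in the same paragraph. One fair reading is therefore a binary score for starting and a continuous score for amount, which is close to what is asked for here. Covariate adjustment is planned where balance fails, and in the continuous-outcome runs direct adjustment for the confounders brought slope bias to about zero (by construction, since that model was correct).

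Much of this stands. A reader might infer that the protocol commits to one density for all women, that five women in six are known to be unexposed, or that the score is the only control of baseline confounding. The text supports none of these: the first is an inference, 5:1 is a planning ratio, and the covariate back-up exists.

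What does not stand is that this settles the matter. The stated reason for the method, that exposure is continuous, does not fit the population the protocol defines, and nothing limits the score to users. The matching is a separate contrast and does not repair the score inside the dose-duration and threshold models. The back-up acts only on imbalance that is detected. A check pooled over all women can miss it, as the near-zero correlations in step 2 show.

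**Conclusion.** The point holds as a mismatch between method and exposure. As written, a continuous-density score is applied to an exposure with a point mass at zero, and this can distort the dose-response upward or downward.

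It is tempting to go further and say that the score will create a false association of a given size, or one comparable with the ±0.2 in the power statement. The documents do not support that: they give no confounding strengths and no scale for ±0.2. The simulation used a quadratic outcome model, not the planned Fine and Gray threshold models, and part of the distortion comes from that quadratic form and not from the zeros. Used as a weight, the same score reduced bias. Only the direction, and the fact that bias can rise as well as fall, should be relied on. The conclusion does not hinge on 83%, since the pattern also appears at 60% zeros.

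**What to change.** State that the continuous score is not fitted across the zeros, and choose one of two routes:

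- **Two-part score** in the dose-duration and threshold models: a logistic model for any CCB use, and a log-normal or gamma density for dose-duration among users.
- **Score among users only**, with a stated rule for joining that curve to the binary none-versus-any analysis. Removing the zeros is not a full cure: in the simulation the users-only score with a quadratic outcome model still left about 0.4 to 2.8 points of bias.

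Under either route, check covariate balance separately for any versus none and across dose among users. Apply the covariate adjustment already planned to whatever remains unbalanced in either check.

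The cost is a change of wording and one extra model per cohort. If the score is used as weights, some may need truncation, and that rule should be set in advance.

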**Methods and analysis:**

The study will use data from 2 of Australia’s largest cohort studies; the Australian Longitudinal Study on Women’s Health, and the 45 and Up Study, combined with the Rotterdam Study. Eligible women will be those with diagnosed hypertension, no history of breast cancer and no prior CCB use at start of follow-up (2004–2009). Cumulative dose-duration exposure to CCB and other AHT medicines will be captured at the earliest date of: the outcome (a diagnosis of invasive breast cancer); a competing risk event (eg, bilateral mastectomy without a diagnosis of breast cancer, death prior to any diagnosis of breast cancer) or end of follow-up (censoring event). Fine and Gray competing risks regression will be used to assess the association between CCB use and development of breast cancer using a generalised propensity score to adjust for baseline covariates. Time-varying covariates related to interaction with health services will also be included in the model. Data will be harmonised across cohorts to achieve identical protocols and a two-step random effects individual patient-level meta-analysis will be used.

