### Statistical analysis

*Primary aim:* for the primary aim, analysis of the association between CCB use and the development of breast cancer will be undertaken using Fine and Gray competing risks regression with incident breast cancer as the principal event, and death (from causes other than breast cancer) or bilateral mastectomy as the competing risk.^47^ In this setting, the appropriate estimate of the probability of breast cancer is described by the cumulative incidence function rather than an HR. The models will account for confounding factors at entry using propensity scores to balance these factors across exposure status captured over the follow-up period. In addition, we will use standard covariate adjustment for time-varying covariates and any covariates that cannot be balanced using the propensity score. Any significant shifts in practice will be identified via the literature (and our clinical collaborators) and included as categorical variables in the models where appropriate.

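### The supplementary exposed-versus-non-exposed matched comparison does not carry over the plan's immortal-time safeguard, so it is biased towards apparent protection by CCBs

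*Protocol article*

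**What the plan says.** All references are to the Protocol article.

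- **Entry.** The Abstract requires "no prior CCB use at start of follow-up", and Study population excludes women with "evidence of CCB use prior to entry". Time zero is the survey or interview date: "Entry to our study will be on survey completion date for women who participated in the ALSWH survey waves between 2004 and 2008", with matching rules for the 45 and Up and Rotterdam cohorts. It is not the date of first CCB dispensing.
- **Exposure label.** Statistical analysis adjusts for factors at entry by using "propensity scores to balance these factors across exposure status captured over the follow-up period". Exposure ascertainment defines four states by use during follow-up, one of them being "women exposed (at any time) to both CCBs and AHTs".
- **Safeguard.** Exposure ascertainment introduces a time-varying, continuous measure of cumulative exposure with the words "To compensate for immortal-time bias".
- **Binary comparison.** Statistical analysis then specifies "standard binary propensity score matching of those exposed versus non-exposed". Its declared purpose is a contrast in which never-users of CCBs "will also be analysed as a baseline to show the impact of no versus any treatment". For this comparison it gives no time-varying status, no landmark and no time zero at initiation.

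**The concern.** No woman is a CCB user at time zero, so the exposed label can come only from a later dispensing. A woman who develops breast cancer or dies before she would have started a CCB is counted as non-exposed. A woman labelled exposed cannot have had either event before her first dispensing. Her pre-dispensing time, event-free by construction, is credited to CCB use, while the matching early events go to the comparator. A propensity score built on entry covariates balances who the women were at entry. It cannot balance a label that depends on surviving to a later date.

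The bias runs towards protection. In a drug-safety study that is the awkward direction: the Discussion says that finding no association would reassure women about CCBs as first-line therapy.

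**Working it through.** **The plan's own figures.** The article gives no figure for immortal-time bias. Its one design figure (80% power, 95% confidence, effect ±0.2, 5:1 unexposed to exposed) cannot be reproduced, because the exposed counts are in Figure 3, which is not shown, and the scale of ±0.2 is not stated.

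**Inputs from the article.** Exposed share f = 1/6 (5:1, Sample size calculation); follow-up of up to 19 years (Discussion); Fine and Gray regression with death or bilateral mastectomy competing (Statistical analysis).

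**Assumed inputs.** Breast cancer 0.35% per year; death 0, 1, 3 or 8% per year; follow-up 10, 14 or 19 years; the pattern of CCB initiation. The true effect is null throughout.

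**Step 1: closed form.** Let w be the mean share of an ever-user's follow-up that precedes her first CCB, and λ the common rate of a rare event. Labels are counted from entry.

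- Exposed rate: λ(1 − w).
- Non-exposed rate: λ[1 − f(1 − w)]/(1 − f), because all events before initiation fall here.
- Ratio: RR = (1 − w)(1 − f)/[1 − f(1 − w)].

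Here f is the ever-exposed share of the cohort from which matches are drawn, not the matching ratio. For f = 1/6 and w = 0.5: 0.5 × 0.8333/(1 − 0.0833) = 0.4167/0.9167 = 0.455.

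| w | 0.05 | 0.1 | 0.2 | 0.3 | 0.4 | 0.5 |
|---|---|---|---|---|---|---|
| RR under the null | 0.94 | 0.88 | 0.77 | 0.66 | 0.56 | 0.455 |

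**Step 2: simulation with competing deaths.** There were 1.5 million women per scenario, with ever/never labels counted from entry and no covariates (equivalent to perfect balance at entry). Constant initiation was tuned to a 1/6 exposed share, leaving about 48% of ever-users' follow-up before first use. Early initiation had a mean of 2 years, with 17 to 20% exposed. Ranges run over the three follow-up lengths.

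| Initiation | Deaths per year | Cause-specific HR | Fine and Gray SHR |
|---|---|---|---|
| Constant | 0% | 0.46–0.47 | 0.46–0.47 |
| Constant | 1% | 0.46–0.47 | 0.49–0.50 |
| Constant | 3% | 0.46–0.47 | 0.52–0.57 |
| Constant | 8% | 0.45–0.46 | 0.60–0.72 |
| Early | 0% | 0.77–0.87 | 0.77–0.87 |
| Early | 1% | 0.77–0.84 | 0.79–0.86 |
| Early | 3% | 0.74–0.84 | 0.78–0.89 |
| Early | 8% | 0.73–0.82 | 0.84–0.96 |

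Every scenario falls below 1. Mortality weakens the bias under Fine and Gray because women who die before starting a CCB are labelled non-exposed yet stay in the risk set, which lowers the comparator's subdistribution hazard.

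**Step 3: the same data with time-varying exposure.** Counting time before the first CCB as unexposed gives person-time rate ratios of 0.98 to 1.01.

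**Step 4: could a real harm be masked?** With w = 1/7 (about 1.4 years of an assumed 10) and f = 1/6, RR = (6/7 × 5/6)/(1 − 1/7) = (5/7)/(6/7) = 5/6 = 0.83. On the rate-ratio scale a true 1.2 would then read 1.2 × 0.83 = 1.00. This is an illustration only: neither w nor the meaning of ±0.2 is given.

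**The case against.** The strongest defence is that the sentence describes a score and a matching method, not a time zero. The article condenses a fuller plan, it cites a method that is not at hand, and Exposure ascertainment introduces time-varying exposure for both aims. The matched analysis might therefore handle timing properly. That remains possible, but the text does not say so. The only entry date it gives is the survey or interview, the comparison is called standard and binary, and the immortal-time remedy is attached to a continuous measure. The time lags under Sensitivity analyses run from the start of follow-up, not from first dispensing, so they do not fill the gap.

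Four stronger readings are tempting, and the documents do not support them:

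- **That a null effect will look like a halving of risk.** This needs initiation spread evenly over follow-up and, under Fine and Gray, low mortality. The article gives neither the timing of first use nor mortality.
- **That the main analysis shares the fault.** A reader might infer this from the Abstract, which captures cumulative exposure at the end of each woman's follow-up. Exposure ascertainment, however, makes that measure time-varying precisely because of immortal time.
- **That this is the plan's only information on no use versus use.** It is presented as an additional analysis, and never-exposed women also enter the dose-duration model.
- **That it would hide a harm of the size the study is powered for.** The scale of ±0.2 is unstated, so 'could mask a modest harm' is as far as one can go.

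**Conclusion.** The point holds for the supplementary no-versus-any comparison. As written, it labels women by CCB use that can begin only after entry, and the plan's safeguard is not carried over to it. The direction is firm: under a true null the result is biased towards protection in every scenario examined.

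The size is conditional: about 0.45 to 0.50 with even initiation and low mortality, and up to about 0.96 with early initiation and high mortality under Fine and Gray. The range rests on the 5:1 ratio from the article (17 to 20% exposed in the early-initiation runs) and on assumed event rates, mortality, follow-up and, above all, timing of first CCB use.

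**What to change.** In Statistical analysis, replace the fixed exposed/non-exposed label by one of these:

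1. **Time-varying binary CCB exposure**, with time before the first dispensing counted as unexposed. This is the simpler option and agrees with Exposure ascertainment. The 0.98 to 1.01 in the working is on the person-time rate scale. If Fine and Gray is kept, state how exposure is defined for women who remain in the risk set after a competing event, since that case was not simulated.
2. **Matching at initiation.** Match each initiator, at her first dispensing, to women in the same cohort who are alive, cancer-free and still CCB-naive at the same time since entry. Start follow-up for both on that date. This removes the immortal period by design but was not simulated.

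Update only the covariates available over time (age, statins, hormone use, Rx-Risk). Keep the others, such as BMI, diabetes and heart disease, at baseline, because Covariates lists them as captured only then for the harmonised analysis.

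Cost: revised wording and some extra programming. Dispensing dates are already held. There is less exposed person-time, because time before initiation no longer counts as exposed. If matched comparators are censored when they start a CCB, the censoring may be informative and should be examined.
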